#### **Limitations to the analyses included in this SAP:**

- Sh1 and Sh2 studies to be conducted in Niger had to be redesigned because of a failure to randomize appropriately and will not be considered further in this SAP. Thus, there are no Sh1 studies covered in this SAP.
- Adverse events during MDAs were recorded by those administering the drugs in a manner consistent with WHO or country guidelines. These records were not requested as part of the SCORE research. Therefore, the planned SAP analyses do not include a "safety" component.
- Requested cost data were not recorded in a systematic manner across countries. Therefore, the SAP analyses do not include any cost-effectiveness components.

### b. Overview of SCORE Cohort studies of infection-associated morbidities

In addition to the Gaining and Sustaining studies, Cohort studies were started in a minimum of 8 randomly selected villages participating within each of the SCORE Sh2 and Sm2 projects, in order to determine whether the intensity of village-level MDA intervention affects measures of health and well-being among school age children. The overall goal of these studies is to provide information to policy- and decision-makers about the actual impact on morbidity of alternative strategies to multi-year MDA with praziquantel in schistosomiasis-endemic areas. Because Niger did not randomize according to the study protocol, and because of poor participation and large loss to follow-up in Mozambique, only data from Kenya and Tanzania Sm2 Cohort studies are available for analysis. Thus, no longitudinal cohort study data are available for Sh, and Sh morbidity will not be considered further in this SAP.

### c. Study design: Gaining and Sustaining studies

**Overview:** The Gaining and Sustaining studies are parallel cluster-randomized, open-label operational research trials of praziquantel MDA for control of prevalence and intensity of *Schistosoma* infections in endemic communities in Africa.

**Study Arms:** Study 1 has three study arms arranged as follows:

[figure not shown]

Study 2 for both species has six study arms arranged as follows:

[figure not shown]

Note that Arms 1, 2, and 3 in Study 1 correspond to Arms 4, 5, and 6 in Study 2. Holidays indicate years in which a village did not receive MDA with praziquantel. No testing of children was conducted during holiday years; otherwise, infected children would have required treatment, which would have precluded evaluation of the impact of MDA holidays.

Because six villages in Mozambique had their cross-sectional study arm re-assigned after randomization (see Appendix L for Protocol Deviations), the initial analysis of treatment outcomes will be “as treated.” Children included in analysis are those who are an “available case,” that is, someone who provided age and sex information and at least one slide for evaluation of infection status.

**Populations and expected sample size:** The goal of each country study was to enroll 25 eligible villages per study arm, and to monitor each village’s prevalence and intensity of *Schistosoma* infection (whether Sm or Sh) among a **random sample of 100 resident 9-12 year-old children each year**, starting before implementation of MDA (Year 1) and continuing through Year 5 (see study arm schema above). Nominal enrollment for each Study 1 was 75 villages, with 7,500 children tested each year. Nominal enrollment for Study 2 was 150 villages, with 15,000 children tested each year.

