3. *Determine eligibility.* Determine eligibility of communities/villages by testing 50 school children in classes that include those ages 13-14. Each Study 1 will require a total of 75 villages (25 per study arm), and each Study 2 will require 150 villages (25 per study arm). Children who test positive in this initial survey should be treated. This will involve examining a mid-day urine in Sh villages, using either dipsticks or 2 filtrations of 10 ml each. In Sm villages this will involve testing a single stool, examining 2 slides per stool.

4. *Randomize.* After an adequate number of eligible communities/villages are identified, they will need to be randomly assigned to the arms of the study – 3 arms for a Study 1 and 6 arms for a Study 2. Regardless of the outcome of randomization, for example, an uneven distribution of a particular factor, villages may not be re-randomized.

[figure not shown]

[figure not shown]

There will be no stratification for randomization of Sh1 and Sm1 communities/villages. Sh2 and Sm2 communities/villages will be randomized with stratification by prevalence on initial screening using Proc Plan, according to an agreed-to protocol.

5. *Identify villages for layered studies (Sh2 and Sm2 only).* Layered studies include subtle morbidity, snail, and parasite genetics evaluations. Investigators funded under this RFP who are conducting Sh2 and Sm2 studies will also be funded to conduct subtle morbidity studies. Investigators funded under this RFP should participate with investigators conducting snail and schistosome population genetics studies to ensure snail collection and plans for parasite collection are in place before MDA.

6. *Sensitize communities.* A greater level of effort will be required to engage eligible communities in the full, multi-year study than was required for the initial eligibility survey. A simple standard approach will be developed to capture what activities are conducted to achieve sensitization.

7. *Train workers.* This includes training on data collection, drug delivery, reporting of adverse events, etc. Incentives may be paid in accordance with local practices and practices of non-government organizations in the area.

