In addition to 9-12 year-old children, SCORE studies included some data collection on first-year students and, in Sh2 and Sm2 studies, in adults. More information about data collected from these populations is provided in the protocols and in Appendix D. Their results are not considered in this SAP, but may be used for future secondary analyses of the SCORE gaining and sustaining studies.

Data are available for the following studies:

- Sm1: Cote d'Ivoire, Kenya
- Sm2: Kenya, Tanzania
- Sh2: Mozambique

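### The SAP makes an as-treated analysis the initial one because six Mozambique villages changed arm after randomisation, and it plans no analysis by randomised arm

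*Combined protocol and SAP*

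**What the plan says.** Section II.c of the main SAP describes the studies as "parallel cluster-randomized, open-label operational research trials of praziquantel MDA". The same section then gives the analysis rule. The reason is "Because six villages in Mozambique had their cross-sectional study arm re-assigned after randomization", and the consequence is that "the initial analysis of treatment outcomes will be “as treated". The rule names no country. It sits in the design section shared by every study under this SAP. Section II.a lists these as "Sm1: Cote d'Ivoire, Kenya", "Sm2: Kenya, Tanzania" and the *S. haematobium* Study 2 in Mozambique.

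Children are analysed as available cases, each being "someone who provided age and sex information and at least one slide for evaluation of infection status".

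The SAP does not define as-treated, and no later analysis follows the one called initial. In section VI.b, Table 4 holds the primary outcomes. The models behind it use the variable Study_Arm on Year 5 data, and neither the text nor the sample code says whether Study_Arm is the randomised or the received arm. Section II.c refers to Appendix L for the deviations; its contents are not in the document reviewed here.

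**The concern.** A cluster-randomised trial supports a causal comparison because chance decided which villages went to which arm. Once villages are counted in an arm they were moved to, that protection is lost for every contrast that involves them. If the reason for a move was related to transmission, access or cooperation, the received arms can differ for reasons other than the treatment strategy.

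Three features of the plan raise the stakes in Mozambique:

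- The Table 4 models use Year 5 data only, unadjusted or adjusted for age and sex. Baseline prevalence is not in the model, so imbalance brought in by the moves is not corrected.
- Section VI.a leaves p-value cutoffs unadjusted and bases interpretation on the strength of the arm effects. A bias in the effect size would pass straight into the conclusions.
- Mozambique is the only *S. haematobium* study under this SAP, so no other study under it can confirm or contradict the result.

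**Working it through.** **1. Nominal size (SAP II.c).** Study 2 has 6 arms of 25 villages and 100 children per village: 6 × 25 = 150 villages and 150 × 100 = 15,000 children, as stated. Study 1 has 3 × 25 = 75 villages. The five studies total 2 × 75 + 3 × 150 = 600 villages.

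**2. Share affected.**

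- Mozambique: 6/150 = 4%.
- One two-arm comparison: at most 6/50 = 12%.
- One arm: at most 6/25 = 24%.
- All five studies: 6/600 = 1%.

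These shares use nominal enrolment. Section VIII gives 52 children as 0.9% of those tested in Mozambique in Year 1, which implies 52/0.009 ≈ 5,800 children. The text does not say how much of the gap to 15,000 is fewer villages. Fewer villages would make the shares larger.

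**3. Which studies are touched.** The only arm changes described are the six in Mozambique. For Kenya, section VIII says the weaker Year 1 community-wide treatment will be discussed but not adjusted for. Villages off schedule are only flagged. Neither passage moves a village between arms. On this text, received and randomised arms coincide in the two Kenya studies, Tanzania and Côte d'Ivoire. The cohort section and the Niger SAP state no as-treated rule.

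**4. How fragile the Mozambique results are (Supplemental Table S3).** SE of the log ratio = (ln upper − ln lower)/3.92.

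| Comparison | Ratio (95% CI) | SE | z | Relative fall that brings the lower limit to 1 |
|---|---|---|---|---|
| SSHH vs SSSS, prevalence | 1.73 (1.08–2.77) | 0.240 | 2.28 | 1 − 1/1.08 = 7.4% |
| CCHH vs CCCC, intensity | 2.15 (1.10–4.18) | 0.341 | 2.25 | 1 − 1/1.10 = 9.1% |

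The last column keeps the interval width fixed on the log scale.

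**5. Possible shift in an arm's mean.** Assumption: m villages join a 25-village arm, with r times its average prevalence. Relative shift = (25 + m·r)/(25 + m) − 1.

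| m | r = 0.5 | r = 2 |
|---|---|---|
| 1 | 25.5/26 − 1 = −2% | 27/26 − 1 = +4% |
| 2 | 26/27 − 1 = −4% | 29/27 − 1 = +7% |
| 6 | 28/31 − 1 = −10% | 37/31 − 1 = +19% |

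This covers the receiving arm only. A village that leaves also changes the mean of the arm it left.

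**6. Gap between the two analyses if the villages are otherwise typical.** Assumption: the ratio by treatment received is truly 1.73, with 25 randomised villages per arm. Let *a* be villages randomised to SSSS that received SSHH, and *b* the reverse. Ratio by randomised arm = [(25 − b) × 1.73 + b]/[(25 − a) + a × 1.73].

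- a = b = 1: 42.52/25.73 = 1.65
- a = b = 3: 41.06/27.19 = 1.51
- a = 6, b = 0: 43.25/29.38 = 1.47
- a = 0, b = 6: 38.87/25 = 1.55

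These are falls of about 4.5% (1 − 1.65253/1.73) to 15% (1 − 1.472/1.73). Here the gap is dilution, not bias, but it spans the 7.4% margin in step 4.

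**The case against.** The strongest reply is that the problem is small and partly handled. Six of 150 villages in one of five studies is a minor departure, and the SAP discloses it and points to an appendix. The SAP calls the analysis initial and describes its contents as a minimum. It sends investigators to the CONSORT extension for cluster trials and requires a flow diagram by arm. Operational researchers may also reasonably want the effect of the strategy that was delivered.

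Much of this stands as a limit on scope. It does not supply the missing analysis: no comparison by randomised arm is named, and an analyst who follows the plan as written would not produce one. The effect of the delivered strategy is a fair supplementary question, but its answer does not have the protection of randomisation.

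A reader might infer three stronger things that the documents do not support:

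- **That none of the five studies compares randomised groups.** The rule is worded for all five, but re-assignment is documented only in Mozambique.
- **That the protocol forbade the moves.** It says "Regardless of the outcome of randomization, for example, an uneven distribution of a particular factor, villages may not be re-randomized", and SAP II.a likewise rules out a second randomisation prompted by the result of the first. Both address a repeat draw. Neither addresses moving a single village.
- **That bias has been shown.** The reasons, timing and direction of the moves are not visible, so bias is a risk only.

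**Conclusion.** The concern holds for Mozambique. Under the plan as written, its comparisons that involve the six villages are not between groups as randomised, and no analysis by randomised arm is planned to show whether that matters. In the other four studies the rule changes nothing on the visible text, so the correction there is one of wording.

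The size is unknown. The shares of 4% and at most 12% rest on nominal enrolment. The shift of −2% to +19% rests on an assumed prevalence ratio of 0.5 to 2 and on one to six villages joining the same arm. The upper end needs all six in one arm, which the text neither states nor excludes. Set against margins of about 7% and 9%, the two significant Mozambique ratios could change status if the villages fall in those comparisons. Whether they do cannot be determined from the text. Table S3 does not say which assignment it used; this reasoning assumes that the SAP was followed.

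**What to change.** 1. In SAP II.c, state that the primary analysis places each village in the arm to which it was randomised, in every study.
2. Keep the as-treated analysis as a sensitivity analysis for Mozambique, and define the term.
3. In section VI.b, state that Study_Arm in the Table 4 models holds the randomised arm.
4. In the Mozambique flow diagram (Figure 2), show the original and final arm of each of the six villages, with the reason for and timing of the move.

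The cost is a few sentences, one arm variable and a re-run of the Mozambique models. This assumes that the original assignment and the Year 5 data are held for the six villages, which the documents do not confirm. If either is missing for a village, report that and state how the village is handled. No other study's models need re-running unless Appendix L records further arm changes.

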#### d. Study design: Cohort studies of *Schistosoma*-associated morbidity

**Overview:** The Cohort studies are sub-studies within SCORE Gaining Control studies, i.e., in communities with  $\geq 25\%$  prevalence of schistosomiasis during eligibility testing. They involve only Arms 1 and 6 of the Gaining Control studies, selected to represent the most intensive and a much less intensive intervention sequence, respectively (see below). Enrolled children were followed for five years, with evaluation occurring at Years 1 (baseline), 3 (after two MDA treatments), and 5 (after four MDA treatments).

**Cohort study design and expected sample size:** Cohort studies aimed to enroll 100 children from at least 4 communities/villages in each study arm, for a total of 800 children per study. The two Sh2 cohorts were discontinued: Mozambique because of significant loss to follow-up and Niger because of inappropriate randomization.

| Cohort Study | Year 1 | Year 2 | Year 3 | Year 4 |
|--------------|--------|--------|--------|--------|
|--------------|--------|--------|--------|--------|

[figure not shown]

Villages for inclusion in this study were meant to be a random sample of all the villages in the two study arms of interest (Arms 1 and 6); however, to facilitate the survey work investigators were allowed to select them randomly from among a restricted group of no less than 10 out of the 25 villages in each arm, chosen, for example, to exclude very remote villages.

The protocol called for selecting the 100-child cohort from the school class that starts at 7 or 8 years of age. If there were over 100 children in this class, children were to be randomly selected for participation. If this class did not include 100 children, then all of the children in that class should have been enrolled along with a random selection of children in the next older class, in order to reach the total of 100 study subjects.

### III. DATA COLLECTION, AND TYPES OF DATA AVAILABLE

The table in Appendix D describes the data elements available from the SCORE Gaining and Sustaining and Cohort studies.

#### a. Individual-level data in Gaining and Sustaining studies

Parasitological data on *Schistosoma* infection among children ages 9-12 were collected prior to each MDA and a year following the last treatment. No data were collected in villages during a holiday year.

In the Sm studies, duplicate Kato-Katz slides were made from each of three daily stool samples from each individual, and the number of eggs found in each slide was recorded. In the Sh studies, 10 ml of urine from a single well-stirred urine sample for each individual was filtered twice, and each of these two filtrations was examined under the microscope; the number of eggs found in each slide and the corresponding volume of urine filtered was recorded.

Parasitological data were also collected in Years 1, 3, and 5 on children in the first-year class and in Years 1 and 5 on adults (see Appendix D). However, given that data on these populations do not represent the

primary end-points of the SCORE treatment studies, and that the data collected on them are much more limited than that for 9-12 year olds, they will not be reported as primary end-points.

## b. Individual-level data in Cohort studies

**Primary Morbidity Markers:** The following were measured in Years 1, 3, and 5, except for ultrasound, which was to be conducted in Years 1 and 5. Kenya chose to perform abdominal ultrasounds in Year 3 as well. All the markers will be available in the SCORE uniform datasets (SUDS) as described in section IV. For details on variable coding, please refer to Appendix F of this SAP: 'Data Dictionary for SCORE Cohort Studies.'

1. Height in cm and weight in kg transformed to age-adjusted Z-scores for each outcome using established WHO/CDC standards, and presence or absence of stunting or wasting.
2. Blood hemoglobin (Hb). While collection of a venous sample was preferred, finger prick capillary blood was acceptable. Based on WHO criteria, at sea level and up to 1000m elevation, anemia is defined as Hb < 11.5 g/dL for age < 12 years, Hb < 12 for females > 12 years, Hb < 12 for males 12-15, and Hb < 13 for males > 15. Altitude-related changes in normal circulating hemoglobin levels require adjustment of anemia cutoffs for higher elevations. The cutoffs are 0.2 gm/dL higher for each age group in Tanzania and Kenya locations as they are located at 1000-1250m elevation [1].
3. Physical fitness (VO2) based on the 20-meter shuttle run protocol. VO2 is calculated as follows:
  - (1) Speed =  $8 + .5 \times \text{No. shuttles successfully completed}$ ;
  - (2)  $\text{VO2} = 31.025 + 3.238 \times \text{Speed} - 3.248 \times \text{Age in years} + .1536 \times \text{Speed} \times \text{Age in years}$ .
4. Measures of well-being based on the standardized questionnaire, PedsQL. This instrument was translated and validated prior to local use. The Physical and other subscale scores for PedsQL were based on child's graded responses to each question. Scale scores were calculated by 1) reversing item answer scores and linearly transforming to a 0-100 scale [0=100, 1=75, 2=50, 3=25, 4=0], and 2) for each subscale, adding transformed scores and dividing by number of items scored. If over 50% of items in the subscale are missing, the subscale is coded as missing. C in the variable name indicates child responses, P indicates parent.
5. Abdominal ultrasound in Years 1 and 5. (Detailed information on variable coding can be found in Appendix F.)

**Infection status (Secondary markers):** All children in the cohort were to be tested in Years 1, 3, and 5 for *S. mansoni* infection. For all children in Sm2, 3 stools were examined using Kato-Katz, 2 slides per stool. For accurate calculation of age-in-months used in anthropometric scoring, exact date of birth was to be ascertained for all participating cohort children.

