## VII. STUDY QUESTIONS AND END-POINTS OF INTEREST FOR COHORT STUDIES

### a. Key research questions

The primary research questions in the cohort studies relate to comparisons of outcome measures between arms at Year 5, and the change from baseline and follow-up, by arm. The primary research questions are:

- 1a. Do morbidity markers among cohort children at Year 5 differ by study arm?
- 1b. How do changes in morbidity markers among cohort children from baseline to follow-up differ by arm?

Interpretation of the results of these analyses needs to be done in the context of the data on prevalence and intensity in the two arms. If data are available on malaria and other factors that could affect morbidity findings, these should be evaluated as well.

Further exploratory analysis should evaluate differences in morbidity by infection intensity. For example, in any given year, is there a relationship between intensity and morbidity measurements? Is there a relationship between changes in individual's intensity over time and changes in their morbidity measures? Note that some outcomes (e.g., liver pattern C) should be assessed taking cumulative exposure into account, whereas others are more likely to be related to contemporaneous exposure.

SCORE is committed to ensuring that the link between intensity and morbidity outcomes is evaluated. However, this is beyond the scope of the core SAP.

The original statistical analysis plans for evaluating the Cohort studies is found in Appendix J.

The following outcomes are of primary interest:

- 1.a. Height and/or weight, as calculated using WHO/CDC age-standardized Z-scores for height (HAZ), weight (WAZ) and body mass index (BAZ); these are typically treated as continuous outcomes.
- 1.b. Growth stunting (HAZ < -2) or nutritional wasting (BAZ < -2) as categorical outcomes.
- 2.a. Hb levels (continuous).

- 2.b. Anemia (categorical). Based on WHO criteria, anemia is defined as Hb < 11.5 g/dL for age < 12 years, Hb < 12 for females > 12 years, Hb < 12 for males 12-15, and Hb < 13 for males > 15. Altitude-related changes in normal circulating hemoglobin levels require adjustment of anemia cutoffs for higher elevations. The cutoffs are 0.2 gm/dL higher for each age group in Tanzania and Kenya locations as they are located at 1000-1250m elevation [1]
3. Maximum oxygen uptake, VO2 max (continuous) estimated based on shuttle run scores.

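### Two cohort outcomes of primary interest have derivation rules that fail if applied literally: VO2 uses a shuttle count as its speed step, and anaemia has no cut-off for girls aged 12

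*Combined protocol and SAP*

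**What the plan says.** **VO2.** Section III.b of the main SAP lists "Physical fitness (VO2) based on the 20-meter shuttle run protocol" among the cohort morbidity markers. It computes Speed as 8 plus 0.5 times the "No. shuttles successfully completed", then puts Speed and age into a regression equation for VO2. It gives no unit for Speed, no definition of a shuttle, and no cap or range check. Section VII.a lists the result among the outcomes of primary interest: "Maximum oxygen uptake, VO2 max (continuous) estimated based on shuttle run scores". Section III.b refers the reader to Appendix F, the cohort data dictionary, for variable coding.

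**Anaemia.** Section III.b sets the cut-offs as "Hb < 11.5 g/dL for age < 12 years, Hb < 12 for females > 12 years, Hb < 12 for males 12-15", with a further band for males over 15. All are raised by 0.2 g/dL for altitude in Kenya and Tanzania. Section VII.a repeats the rule for the primary-interest outcome, again with "Hb < 12 for females > 12 years". Section II.d draws the cohort "from the school class that starts at 7 or 8 years of age", topped up from the next older class where needed. The arms are compared at Year 5.

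**The concern.** The SAP preface requires its definitions to be used in analysis, so a literal reading is a legitimate one.

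For VO2, a shuttle in a 20-metre shuttle run is naturally read as one 20 m length. On that reading the speed fed into the equation soon stops describing a child's running pace, and differences between arms are on a false scale. The two cohort countries could also enter different quantities, lengths in one and levels in the other, and both would be following the SAP.

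For anaemia, girls aged 12 are the only sex-and-age group without a cut-off, and 12 is an age many cohort children reach by Year 5. Baseline is almost untouched, so the gap falls on one sex at follow-up. It enters both the Year 5 comparison and the Year 1 to Year 5 change analysis, and the SAP uses anaemia as its worked example for both (Tables 4A and 5A).

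**Working it through.** The documents state no VO2 value or anaemia count that depends on these rules, so there is no figure to reproduce. The check evaluates the rules as written.

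**VO2: inputs (Section III.b).** With N the multiplier and A age in years:

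- Speed S = 8 + 0.5N
- VO2 = 31.025 + 3.238S − 3.248A + 0.1536·S·A

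**Results at A = 10, with N counted as 20 m lengths** (lengths per child are not in the documents; 20 to 40 is assumed):

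- N = 20: S = 18; 31.025 + 58.284 − 32.480 + 27.648 = 84.5
- N = 30: S = 23; 31.025 + 74.474 − 32.480 + 35.328 = 108.3
- N = 40: S = 28; 31.025 + 90.664 − 32.480 + 43.008 = 132.2

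If Speed is in km/h (the unit is not stated), 28 km/h is 28/3.6 = 7.78 m/s. That is 20 m in 20/7.78 = 2.6 s, after only 40 × 20 = 800 m in total.

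**Age effect.** The change in VO2 per year of age is −3.248 + 0.1536S. It is zero at S = 3.248/0.1536 = 21.1, that is N = (21.1 − 8)/0.5, or about 26. Above that, an older child with the same count scores higher than a younger one, the reverse of the equation's behaviour at lower speeds.

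**Small multipliers.** For N from 1 to 10, S runs from 8.5 to 13.0, and VO2 at age 12 runs from 35.2 to 58.1.

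**The same child under both readings.** Assume one-minute stages at 8 + 0.5k km/h (not in the documents). Stage k then holds (8 + 0.5k) × 1000/60/20 lengths: 7.08, 7.50 and 7.92 for stages 1 to 3, which total 22.5. At age 12:

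- Completing stage 3: VO2 is 40.3 from the stage number and 89.9 from 22.5 lengths.
- Completing stage 5 (39.6 lengths): 45.4 and 133.3.

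The step between these two performances is 45.4 − 40.3 = 5.1 on one reading and 133.3 − 89.9 = 43.4 on the other, about 8.5 times as large.

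**Anaemia: cut-offs coded literally, with 0.2 g/dL added.**

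| Age | Girls | Boys |
|---|---|---|
| under 12 | 11.7 | 11.7 |
| 12 | none | 12.2 |
| 13-15 | 12.2 | 12.2 |
| over 15 | 12.2 | 13.2 |

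Enrolment at 7 or 8 plus four years (Year 1 to Year 5) gives 11 or 12 at the comparison. Top-up children from the next class may be older.

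- Age in completed years: every 12-year-old girl falls in the empty cell.
- Decimal age: a girl of 12.01 is already above 12, so only exactly 12.0 is uncovered.

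If an analyst uses an adjacent band, the choice is between 11.7 and 12.2, and only girls with haemoglobin from 11.7 to below 12.2 are affected. With haemoglobin assumed normal (mean 12.0 to 13.0, SD 1.0 to 1.5; not in the documents), that share is Φ((12.2 − mean)/SD) − Φ((11.7 − mean)/SD):

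- mean 12.0, SD 1.0: 0.579 − 0.382 = 0.197
- mean 13.0, SD 1.5: 0.297 − 0.193 = 0.104

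So roughly 10% to 20% of 12-year-old girls would change class.

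**The case against.** On VO2, the strongest reply is that the SAP sends the reader to Appendix F for coding and elsewhere speaks only of shuttle run scores. If the stored field is a level, the derived values are sound and the fault is one loose word. That stands. A reader might infer from the figures above that the cohort VO2 values are wrong; the documents do not show this, because the stored variable is not visible. Calling values implausible also relies on general judgement, since the SAP states no range. The speeds implied by the SAP's own formula carry the argument without it. Nor should a range of lengths be set against an unrelated range of levels as if it were the size of the error. They need not describe the same children, which is why the matched comparison above rests on an explicit stage assumption.

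On anaemia, Section III.b says exact date of birth was to be obtained, so decimal age could be used and the gap would almost vanish. This stands as a possibility. However, the stated purpose of the birth date is anthropometric scoring, and a band written as 12-15 followed by one above 15 suggests completed years. A reader might also infer that 12-year-old girls would be dropped under the complete-case rule in Section VII.c, or counted as not anaemic. That is only one coding outcome. These girls have age and haemoglobin recorded, and an analyst may well place them in a neighbouring band. The documents also do not give the age mix, so no firm share of the cohort can be attached to the gap.

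**Conclusion.** Both rules fail as written, and both outcomes are listed as of primary interest.

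- **VO2:** applied to 20 m lengths, the rule gives 84.5 to 132.2 at age 10 for 20 to 40 lengths, with a reversed age effect above about 26 lengths. It behaves sensibly only for a small multiplier such as a speed level. That the rule needs correcting is clear; that any stored value is wrong is not established and turns on Appendix F.
- **Anaemia:** the missing cut-off for girls aged 12 is certain and appears twice. Its reach depends on the unstated age form: all 12-year-old girls with completed years, almost none with decimal age. If an adjacent band is used, about 10% to 20% of those girls would change class under the assumed haemoglobin distributions.

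The point concerns only the Kenya and Tanzania cohort sub-studies. Prevalence and intensity in 9-12-year-olds are untouched.

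**What to change.** **VO2.** Check which variable Appendix F stores. Define the multiplier in Section III.b as the speed level or stage completed, and state the unit of Speed. If lengths were recorded, convert them to levels using the test's own stage structure, which should be added to the SAP. Recompute VO2 for Years 1, 3 and 5 in both countries, with a stated range check.

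**Anaemia.** In Sections III.b and VII.a, say whether age is in completed years or decimal, and close the band for girls aged 12 consistently with the criteria the SAP cites. Replacing strictly above 12 by 12 and over would match how boys are treated. Apply the same rule in both cohorts.

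**Cost.** A few lines of SAP text, one check of the data dictionary, and a rerun of two derived variables and the cohort tables that use them. No new data are needed unless lengths were recorded without the stage structure.
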